#### 4.3.3. Proportion of gE-Specific CD4+ T-Cells

This is defined with gE-specific CD4+ T-cells expressing ≥ 2 of the 4 activation markers: IFN-γ, IL-2, TNF-α, and CD40 ligand. Assessment will be performed using flow cytometry at Labcorp Central Laboratory Services Limited Partnership, Labcorp Translational Biomarker Solutions. The proportion of gE-specific CD4+ T-cells was calculated as follows: gE-specific CD4+ T-cells/total CD4+ T-cells.

#### 4.3.4. Antibody Titre of VZV-Specific Antibodies

Evaluation of VZV-specific antibodies will be performed using ELISA at the Osaka Metropolitan University.

#### 4.3.5. Changes in RA Disease Activity

RA disease activity will be monitored using the DAS28-CRP, DAS28-erythrocyte sedimentation rate (DAS28-ESR), simplified disease activity index (SDAI), and clinical activity index (CDAI).

If flare is observed, treatment will be at the discretion of each attending physician and will not be limited by this study (Table 1).

### 4.4. Sample Size

Given the design as an exploratory study, the sample size was calculated based on the number of patients at our hospital. In our institution, approximately 1000 patients with RA are being treated, including 300 who are currently receiving MTX monotherapy and 30 who are receiving upadacitinib.

An average of 80 patients receive JAK inhibitors per year, including 40 patients who have initiated upadacitinib therapy (with or without MTX). Therefore, 120 upadacitinib initiations were projected for the 3-year enrollment period. Accordingly, informed consent can be obtained from 40 patients for each group (20 in the MTX combination group, 20 in the upadacitinib monotherapy group). Accounting for a 10% dropout rate, the target enrollment was set at 23 patients for each group (Figure 2).

### 4.5. Recruitment

Eligible patients will be recruited from our hospital. In cases of participant shortage, patients can be recruited from nearby hospitals and clinics.

## 5. Assignment of Interventions: Allocation

### 5.1. Sequence Generation

Not applicable to this study.

### 5.2. Concealment Mechanism

Not applicable to this study.

### 5.3. Implementation

All patients will be assigned to receive Shingrix^®^.

### 5.4. Who Will Be Blinded

The treatment arm of each participant is not disclosed to the outcome assessors for blinded assessment of anti-gE antibodies or gE-specific CD4+ T-cells.

### 5.5. Procedure for Unblinding if Needed

Not applicable to this study.

## 6. Data Collection and Management

### 6.1. Plans for Assessment and Collection of Outcomes

Study data will be collected and managed using REDCap (Research Electronic Data Capture) electronic data capture (EDC) tools hosted at Osaka Metropolitan University. REDCap is a secure, web-based software platform designed to support data capture for research studies, providing (1) an intuitive interface for validated data capture; (2) audit trails for tracking data manipulation and export procedures; (3) automated export procedures for seamless data downloads to common statistical packages; and (4) procedures for data integration and interoperability with external sources.

Humoral and cell-mediated immunogenicity data will be electronically provided by AbbVie Deutschland GmbH and Co KG and the Labcorp Central Laboratory Services Limited Partnership, respectively.

### 6.2. Plans to Promote Participant Retention and Complete Follow-Up

To promote participant retention and complete follow-up, the principal investigator and co-investigators will hold regular meetings once a month to discuss participants who discontinue or deviate from the protocol.

### 6.3. Data Management

All collected data will be stored by the principal investigator or co-investigator using the password-protected EDC system. Data will be double-checked by dedicated monitoring personnel.

### 6.4. Confidentiality

Personal identifiers, including names, initials, and patient IDs, will be removed. Anonymized correspondence tables with new codes will be generated to ensure participant anonymity. These tables will be stored on a password-locked standalone computer, disconnected from the internet and the hospital’s electronic medical record network. Additionally, the principal investigator will store documents related to the study in a lockable storage cabinet for at least 5 years after study completion.

Upon disposal of relevant materials after the storage period, data will be erased from the computer, and paper documents will be disposed using a shredder.

When sending blood samples to research institutions for the evaluation of immunogenicity, only the new code, age, and sex registered in the EDC system will be provided. Details of the treatment will be blinded to the institutions to avoid bias.

### 6.5. Plans for Collection, Laboratory Evaluation, and Storage of Biological Specimens for Genetic or Molecular Analysis in This Trial/Future Use

An additional 6 mL of peripheral blood will be collected, and serum, PBMCs, and RNA extracted from PBMCs will be stored. Currently, we plan to analyze the gene expression related to the pathophysiology of RA and inflammation as an ancillary study into this research. Ancillary research will be conducted once approval from the Ethics Committee and patient consent are obtained.

## 7. Statistical Methods

### 7.1. Statistical Methods for Primary and Secondary Outcomes

#### 7.1.1. Full Analysis Set (FAS)

FAS includes patients who received at least one Shingrix^®^ dose.

#### 7.1.2. Per Protocol Set (PPS)

From the FAS, PPS excludes patients who have seriously violated the protocol, as indicated below:Violation of the inclusion criteria.Exclusion criteria violations.Medication compliance violation (interruption of oral medication for 14 consecutive days).Failure to receive Shingrix^®^ injections.Injection of other vaccines between the time of consent and 4 weeks after the second Shingrix^®^ dose.Dose changes of anti-rheumatic drugs (e.g., MTX, glucocorticoids, upadacitinib) between the time of consent and 4 weeks after the second Shingrix^®^ dose.

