### 3.3. Criteria for Discontinuing or Modifying Allocated Interventions

#### 3.3.1. Criteria for Discontinuing Allocated Interventions

Allocated interventions are discontinued for the following situations:(1)When the patient withdraws the informed consent.(2)When a principal investigator or co-investigator judges that it is difficult to continue the research due to worsening of the primary disease, complications, or the occurrence of serious adverse events.(3)When there is a need to administer contraindicated drugs.(4)When serious deviations from the research protocol occur, such as violations of the Clinical Research Act and its implementation regulations, inclusion, or exclusion criteria. Examples of serious deviations are listed below, but are not limited to these events:
Medication non-compliance: interruption of oral medication for 14 consecutive days.Patients who did not receive at least one dose of Shingrix^®^ as scheduled.Patients who received other vaccines between obtaining informed consent and 4 weeks after the second Shingrix^®^ dose.(5)When pregnancy of the study subject is discovered.(6)When the study is discontinued.(7)When the drugs being administered (MTX and Upadacitinib) are discontinued or are found to have been discontinued prior to intervention.(8)When the principal investigator or co-investigator determines that it is difficult to continue the study.

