### 3.5. Relevant Concomitant Care Permitted or Prohibited During the Trial

Concomitant use of other anti-rheumatic drugs, analgesics, and necessary medications (except other bDMARDs and JAK inhibitors) is permitted. However, dose changes of anti-rheumatic drugs, including MTX, upadacitinib, and glucocorticoids, are prohibited from the time of consent acquisition until 4 weeks after the second Shingrix^®^ dose.

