## 4. Outcomes

### 4.1. Primary Endpoint

Proportion of participants with positive anti-gE antibodies at 4 weeks after the second Shingrix^®^ dose.

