**Figure 2 jcm-13-07321-f002:**
[figure not shown]
Sample size explanation. IC: informed consent, MTX: methotrexate, RA: rheumatoid arthritis, UPA: upadacitinib.

**Table 1 jcm-13-07321-t001:** Participant timeline.

	Before Enrollment	At Enrollment	Week 4	Week 8	Week 12	Week 20
Visit	0	1	2	3	4	5
Allowance			+1 week	+2 week	+3 week * 1	−2~+4 week * 2
Informed consent		X				
Eligibility screen		X				
Shingrix^®^ injection		X		X		
Disease activity of RA	X	X	X	X	X	X
Assessment of adverse events		X	X	X	X	X
Blood tests * 3 Urine tests * 4 Serum storage	X	X	X	X	X	X
Immunogenicity * 5		X	X		X	
Additional blood collection		X	X		X	
Confirmation of concomitant drug	X	X	X	X	X	X
RA flare						X

* 1: 4 weeks + 1 week after the second Shingrix^®^ dose; * 2: 12 weeks ± 2 weeks after the second Shingrix^®^ dose; * 3: Blood tests include white blood cell count, red blood cell count, haemoglobin, platelet count, albumin, aspartate aminotransferase (AST), alanine aminotransferase (ALT), creatinine, blood urea nitrogen (BUN), CRP, and rheumatoid factor (RF); * 4 Urine test results include urine protein and occult blood; * 5 Immunogenicity evaluation includes anti-gE antibody, gE-specific CD4+ T-cells, and VZV-specific antibodies.

**Table 2 jcm-13-07321-t002:** Type of report.

			Regional Bureau of Health and Welfare	Accredited Clinical Research Review Board	
Type of Report			Regular Report	On-Time Report	Regular Report
Pharmaceuticals	Known	Death	〇	15 days	〇
		Serious condition other than death	〇	15 days	〇
		Non-serious	〇	―	〇
	Unknown	Death	〇	15 days	〇
		Serious condition other than death	〇	30 days	〇
		Non-serious	〇	―	〇
Infection	Known	Death/Serious	〇	15 days	〇
		Non-serious	〇	15 days	〇
	Unknown	Death/Serious	〇	15 days	〇
		Non-serious	〇	―	〇

〇 means required, and ― means not required.

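### The PPS exclusion for interrupted oral medication has no time limit, so read literally it drops completed immunogenicity results because of an interruption after the Week 12 sample

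*Protocol article*

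**What the plan says.** Section 7.1.2 forms the PPS by taking out of the FAS patients with serious protocol violations, and lists six kinds. Three of them concern conduct over time:

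- Interrupted medication: "Medication compliance violation (interruption of oral medication for 14 consecutive days"). No start or end is given.
- Other vaccines: "Injection of other vaccines between the time of consent and 4 weeks after the second Shingrix^®^ dose".
- Dose changes: "Dose changes of anti-rheumatic drugs (e.g., MTX, glucocorticoids, upadacitinib) between the time of consent and 4 weeks after the second" vaccine dose.

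Section 3.3.1 repeats the interruption criterion among its examples of serious deviations, again without a period: "Medication non-compliance: interruption of oral medication for 14 consecutive days". Its other-vaccine example does carry an end date. Section 3.5 states that dose changes of anti-rheumatic drugs "are prohibited from the time of consent acquisition until 4 weeks after the second" vaccine dose. Section 4.3.5 leaves the treatment of a flare to the attending physician, without restriction by the study.

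The primary endpoint (section 4.1) is the "Proportion of participants with positive anti-gE antibodies at 4 weeks after the second Shingrix^®^ dose". Table 1 allows that sample a short delay ("1: 4 weeks + 1 week after the second Shingrix^®^ dose") and schedules no later immunogenicity sample. The last visit is 12 weeks, plus or minus 2, after the second dose. The FAS (section 7.1.1) requires only one vaccine dose. Section 7.2 does not name the analysis set for the primary endpoint.

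**The concern.** An analysis set for an endpoint should depend only on what happened up to the time the endpoint was measured. Two of the three time-dependent items in the list respect this for the immunogenicity endpoints. The interruption item, as printed, does not. A patient could take the oral drug without a gap through both vaccinations and the Week 12 sample, stop it for 14 days afterwards, and lose PPS membership for an antibody result already complete.

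What is at stake is selection on an event after the outcome. The three arms are not randomised, and they are defined by the same drugs whose interruption triggers the exclusion. Late interruption could therefore differ between arms and could be related to the patient's condition. With about 20 evaluable patients per arm, one or two removals visibly move a proportion.

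**Working it through.** **Inputs**

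- Primary sample: 4 weeks after the second dose, allowance to 5 weeks (section 4.1; Table 1, footnote 1).
- Last visit: 12 weeks after the second dose, allowance 10 to 14 weeks (Table 1, footnote 2).
- Length of interruption that triggers exclusion: 14 days (section 7.1.2).
- Evaluable patients: 20 in each upadacitinib arm, target enrolment 23 per group after 10% dropout (section 4.4).

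**The plan's own figure.** 20 / (1 − 0.10) = 22.2, rounded up to 23 per group, and 3 × 23 = 69. This reproduces the stated target. It is a feasibility figure, and the present point does not change it.

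**Step 1: can a 14-day interruption lie wholly after the primary sample?** Time available = last visit minus primary sample, both counted from the second dose.

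- Nominal: 12 − 4 = 8 weeks = 56 days.
- Shortest: 10 − 5 = 5 weeks = 35 days.
- Longest: 14 − 4 = 10 weeks = 70 days.

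Even the shortest period exceeds 14 days, so it can.

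**Step 2: what the printed list does with events in that period**

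| Event wholly after the Week 12 sample | End date in 7.1.2 | PPS status, read literally |
|---|---|---|
| Other vaccine | 4 weeks after second dose | Kept |
| Dose change of an anti-rheumatic drug | 4 weeks after second dose | Kept |
| Oral medication interrupted for 14 days | None | Excluded |

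**Step 3: how far a proportion could move.** The counts are assumed, since the article gives no expected positivity rate and no rate of late interruption. Start from 20 evaluable patients and remove two, who are either both positive or both negative.

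| Assumed start | Two positives removed | Two negatives removed |
|---|---|---|
| 12/20 = 60.0% | 10/18 = 55.6% | 12/18 = 66.7% |
| 16/20 = 80.0% | 14/18 = 77.8% | 16/18 = 88.9% |
| 18/20 = 90.0% | 16/18 = 88.9% | 18/18 = 100% |

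For 16/20 the exact (Clopper–Pearson) 95% interval is 56.3% to 94.3%. Every shift in that row lies well inside it. The direction depends on who is removed.

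**The case against.** The strongest reply is that the text is silent on the period; it does not state a long one. A reader might infer that the exclusion is meant to run to Week 20, or to Week 24 with the allowance. No section says so. The article condenses a full protocol that is not shown, and that protocol may set the window. This stands as a limit on the claim. The article does, however, print windows for two neighbouring items and none for this one, so anyone applying the printed list has no stated reason to stop at Week 12.

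The item is also worded as a compliance violation. After the restriction in section 3.5 ends, and with flare treatment left to the physician in section 4.3.5, a physician-directed pause may not count as one. That too stands: such pauses may or may not be caught, and the wording does not settle it.

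The dose-change and vaccine items may be bounded simply because those acts are restricted only up to that time. This explains the difference in the list, but it does not justify dropping a Week 12 result for a later event.

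A longer window could be deliberate, because RA flare and disease activity are followed to 12 weeks after the second dose and a late interruption bears on both. This is a good reason not to apply one cut-off to every endpoint. It is no reason to apply the longer window to antibody and T-cell results.

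Finally, section 7.6.1 lets queried cases be settled by discussion with the statistical analyst and recorded. That gives a route for doubtful cases but no rule.

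**Conclusion.** The concern holds as a defect in the definition of one analysis set. As printed, the interruption exclusion makes PPS membership for the immunogenicity endpoints depend on a period of about 8 weeks (35 to 70 days) after the last immunogenicity sample, while the vaccine and dose-change exclusions do not.

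A reader might go further and conclude that valid primary results are lost to the trial, or that the positivity rates will be biased upwards. The document supports neither. The FAS keeps every vaccinated patient, so a result leaves at most one of two sets, and section 7.2 does not tie the primary endpoint to either. The primary analysis is a descriptive summary in an exploratory study. No rate of late interruption is given, so the size of any bias is unknown, and the illustration moves in both directions. The 8 weeks are 40% of the 20-week schedule (8/20), but that is a share of calendar time, not of expected exclusions.

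The conclusion rests on a literal reading of section 7.1.2 and on there being one PPS for all endpoints, which is all the article defines.

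**What to change.** In section 7.1.2:

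1. For the immunogenicity endpoints (anti-gE antibodies, VZV-specific antibodies, gE-specific CD4+ T-cells), count a 14-day interruption as a PPS exclusion only if it falls between consent and the sample taken 4 weeks after the second dose. Tying the end to the actual sample date covers the one-week allowance. Say how an interruption that spans the sample date is counted.
2. Report later interruptions descriptively by arm, without removing the patient from the PPS for these endpoints.
3. State separately which window applies to the PPS for RA flare and disease activity, which run to 12 weeks after the second dose.
4. Reconcile the analysis-set wording with sections 3.3.1, 3.5 and 4.3.5, including whether a physician-directed pause after the restricted period is a compliance violation for the purpose of the PPS.

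The cost is a PPS definition that differs by endpoint, in a few lines of text. It needs no extra patients or visits, and the target of 23 per group stays as it is. The change concerns only who is analysed in which set; no clinical rule changes.

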### 4.2. Secondary Endpoints

(1)Presence or absence of RA flares from enrollment to 12 weeks after the second Shingrix^®^ dose.(2)Proportion of participants with positive anti-gE antibodies at 4 weeks after the first Shingrix^®^ dose.(3)Antibody titre of anti-gE antibodies at 4 weeks after the first and second Shingrix^®^ doses.(4)Proportion of gE-specific CD4+ T-cells at 4 weeks after the first and second Shingrix^®^ doses.(5)Antibody titre of VZV-specific antibodies at 4 weeks after the first and second Shingrix^®^ doses.(6)Changes in RA disease activity.

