#### 4.3.2. RA Flare

This is defined based on the following: (1) judgment by the attending physician, (2) administration of new or increased dose of glucocorticoids, (3) increased or addition of anti-rheumatic drugs, and (4) increased disease activity based on a Disease Activity Score (DAS)28-C-reactive protein (CRP) ≥0.6. The observation period was set until 12 weeks after the second Shingrix^®^ dose based on previous studies [7,10]. However, an extension of 2 weeks (20 -2 to +4 weeks from the enrollment of the study) is allowed.

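### Flare-treatment rules conflict (3.5 against 4.3.5), and the dose changes that help define RA flare also exclude patients from the PPS, with no analysis set or combination rule stated for flare

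*Protocol article*

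**What the plan says.** The Introduction gives immunogenicity and disease flares together as the study objective. Section 4.2 makes flare the first secondary endpoint: "Presence or absence of RA flares from enrollment to 12 weeks after the second" vaccine dose. With an 8-week dosing interval this is nominally Weeks 0–20.

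Section 4.3.2 lists four components. The first is the attending physician's judgement. The next two are drug escalations: "2) administration of new or increased dose of glucocorticoids, (3) increased or addition of anti-rheumatic drugs". The fourth is "increased disease activity based on a Disease Activity Score (DAS)28-C-reactive protein (CRP) ≥0.6". No reference visit is named for that rise.

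Three other rules bear on the same escalations:

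- Section 3.5: "dose changes of anti-rheumatic drugs, including MTX, upadacitinib, and glucocorticoids, are prohibited from the time of consent acquisition until 4 weeks after" the second vaccine dose, nominally Week 12. No exception is made for flare.
- Section 4.3.5, on what happens if a flare occurs: "treatment will be at the discretion of each attending physician and will not be limited by this study". No time limit is given.
- Section 7.1.2 lists among the serious violations that remove a patient from the PPS: "Dose changes of anti-rheumatic drugs (e.g., MTX, glucocorticoids, upadacitinib) between the time of consent and 4 weeks after the second" vaccine dose.

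Section 3.3.1 also allows the intervention to be stopped when an investigator finds it "difficult to continue the research due to worsening of the primary disease, complications" or serious adverse events. The FAS (7.1.1) and SAS (7.1.3) keep everyone vaccinated at least once. Section 7.3 summarises flare by group and names no analysis set.

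**The concern.** The same act, raising a glucocorticoid or anti-rheumatic drug dose for a flare before Week 12, is treated in four ways. It is evidence of the outcome (4.3.2), a prohibited act (3.5), an act the study does not restrict (4.3.5) and a reason for exclusion from the PPS (7.1.2). An attending physician facing a flare at Week 6 cannot satisfy both 3.5 and 4.3.5.

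For the analysis, exclusion from the PPS depends on the outcome being measured. A PPS flare proportion would be too low, and by different amounts in the three arms if flare frequency or the habit of escalating differs between them. Flare is the RA-specific harm the study sets out to describe, so a low rate produced by exclusions or by a definition that is hard to meet would mislead.

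**Working it through.** **Plan's own figures.** The documents give no expected flare rate. The only calculated figure is the sample size in Section 4.4: 20 per group with 10% dropout gives 20/(1 − 0.10) = 22.2, rounded up to 23 per group and 69 in total. This reproduces. The 20 per group is used below only for scale.

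**Overlap of windows.** The ban and the PPS exclusion run to nominal Week 12; flare is counted to nominal Week 20. Overlap: 12/20 = 60%. With the 10-week dosing interval allowed in 3.3.2 it is 14/22 = 64%. With the upper visit allowances in Table 1 it is 15/24 = 62.5%.

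**Effect on a PPS flare proportion.** Let *p* be the true flare proportion, *w* the share of flares inside the window and *t* the share of flares treated by a dose change. Assume timing and treatment are independent and no other exclusions apply. A fraction *tw* of flaring patients leaves both numerator and denominator:

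PPS proportion = *p*(1 − *tw*) / (1 − *p·tw*)

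None of *p*, *w* and *t* is in the documents. Taking *w* = 0.60 (flares spread evenly) and *t* = 0.5 to 1:

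| True *p* (FAS/SAS) | PPS, *t* = 0.5 (*tw* = 0.30) | PPS, *t* = 1 (*tw* = 0.60) |
|---|---|---|
| 10% | 0.07/0.97 = 7.2% | 0.04/0.94 = 4.3% |
| 20% | 0.14/0.94 = 14.9% | 0.08/0.88 = 9.1% |
| 30% | 0.21/0.91 = 23.1% | 0.12/0.82 = 14.6% |

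For 20 patients and *p* = 20%, the expected count falls from 4 flares in 20 patients to 2.8 in 18.8 or 1.6 in 17.6. The PPS proportion reaches 0% only if *t* = *w* = 1. In the FAS or SAS the set definition removes no flare and the proportion stays at *p*.

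**Combination rule.** Section 4.3.2 joins its components with *and*: "2) administration of new or increased dose of glucocorticoids, (3) increased or addition of anti-rheumatic drugs, and (4) increased disease activity".

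- Read as all four required, a flare before Week 12 would generally need a change that 3.5 prohibits. Where the ban is obeyed, early flares would then largely go uncounted in every analysis set.
- Read as any one sufficient, a DAS28-CRP rise of 0.6 counts alone, and the result depends on which visit is the reference.

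**The case against.** A reader might infer that treated flares are removed from the flare analysis by construction. The documents do not support that:

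- No section assigns flare to the PPS, and the FAS and SAS keep these patients. Mapping endpoints to sets is often left to the analysis plan, which is not shown. Excluding dose changes up to Week 12 is also sensible for an antibody endpoint measured then.
- The last 8 of the 20 weeks carry neither ban nor exclusion.
- If one component suffices, flares identified by physician judgement or DAS28-CRP without a dose change stay in the PPS.
- Adding a drug is not clearly a dose change, and 3.5 permits other anti-rheumatic drugs apart from other bDMARDs and JAK inhibitors.
- Dose escalation is not a named trigger in 3.3.1. Nothing says that a flare already recorded is discarded, or that flare follow-up ends on discontinuation; the article is silent.

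It can be added that flare is a descriptive secondary endpoint in an exploratory study, that the Introduction refers to published flare definitions, and that a single flare entry at Week 20 in Table 1 fits a cumulative yes/no outcome.

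All of this stands, and it confines the bias to a PPS-based summary. It does not remove the conflict between 3.5 and 4.3.5, which an analysis plan cannot settle because both are rules for conduct. Nor does it settle how the components listed in 4.3.2 combine.

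**Conclusion.** The concern holds in a limited form. Sections 3.5 and 4.3.5 contradict each other for about 12 of the 20 weeks in which flare is counted. The dose changes at issue are both flare components and PPS exclusions, so any PPS flare summary would be biased downward: a true 20% becomes about 15% to 9%. That range rests on assumed values (60% of flares before Week 12, 50–100% treated by dose change) and shows scale only; it is not an estimate. A FAS or SAS summary is free of this exclusion. The missing any/all rule and the missing DAS28-CRP reference visit affect the flare result in every set. The documents do not establish that flares will in fact be lost from the reported analysis, or that follow-up stops after discontinuation.

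**What to change.** 1. The sponsor must reconcile Section 3.5 with Section 4.3.5 for the period up to four weeks after dose 2. No clinical rule is proposed here.
2. State in Section 7.3 that the flare and disease-activity summaries use the FAS/SAS, with any PPS version supportive only.
3. State in Section 4.3.2 whether any one or all of the components are required and which visit is the reference for the DAS28-CRP rise. Tabulate each component separately by group.
4. State that flare-driven escalation, and discontinuation for worsening RA, are counted in the flare summary.

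Table 1 already schedules disease activity and concomitant-drug checks at Weeks 4, 8, 12 and 20, so no new visits are needed. The cost is wording changes and a little extra tabulation.
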